### Intervention

All patients will be advised (50 min seminar) on the health benefit of exercise according to current guidelines before intervention. We report our intervention according to the TIDieR checklist. After the informed consent and screening steps are completed, patients will be randomly assigned to three groups (in a 1:1:1 ratio): the MICT group, involving moderate-intensity continuous training (MICT); the HIIT group, involving high-intensity interval training (HIIT); and the guideline group, involving guideline-based physical activity (Figure 1). Participant compliance is of paramount importance for this study, and every possible measure will be taken to maintain adherence to the exercise intervention and follow-up plans. If a participant fails to attend three consecutive sessions, the researcher will actively inquire about the reasons for their absence and provide encouragement for continued participation. To account for the minimal effective dose of exercise, a minimum attendance rate has been established based on previous research findings (Abreu et al., 2021). Specifically, participants who complete fewer than 24 training sessions will be classified as dropouts. The adherence to the training program will be meticulously monitored and regularly documented throughout the trial, allowing for comprehensive analysis and evaluation. Reasons for terminating the test: if serious adverse events occur during exercise, the test should be terminated in time. Adverse events: (1) severe hypoglycemia and complications: shaking, dizziness, abnormal sweating, headache, blurred vision, (2) chest pain, arrhythmia, (3) breathing difficulties and asthma.

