### Exclusion criteria

Patients who meet any of the following criteria will be excluded: patients with (1) inability to exercise or other diseases that may affect their physical activity; (2) cognitive disorder; (3) serious comorbidities or complications, such as heart failure, autonomic neuropathy, and recent stroke; (4) a high risk of falling; (5) a history of cancer; or (6) end-stage renal disease dialysis.

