### Training intervention

Participants in the MICT and HIIT groups will perform exercise of different intensity on a treadmill. Exercise intensity, duration, the heart rate (HR), and blood pressure will be recorded before and after exercise, along with any adverse events during exercise. To minimize the risk of bias in the interpretation of the results, we matched the amount of exercise between the HIIT and MICT groups based on workload. Exercise training will be terminated at signs of any serious adverse event (SAE), such as, severe hypoglycemia and complications: shaking, dizziness, abnormal sweating, headache, blurred vision; chest pain, arrhythmia; breathing difficulties and asthma; pain and fatigue.

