### Static balance

Static balance function will be assessed by instructing the participant to stand on one foot with their eyes closed. Impaired static balance is a potential risk factor for fall (Dixon et al., 2017). During the test, participants will be instructed to lift one foot, and the tester will start the timer. The test will continue until the supporting foot moves or the raised foot lands on the ground, indicating the end of the trial. Both legs will be tested three times each to determine the maximum value achieved. To ensure accurate results, a 30-s break will be provided between each test. This break serves to minimize the effects of fatigue and other factors that could influence performance.

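### The two adverse-event lists disagree and neither names falls or injuries, and recording is stated only for treadmill sessions, so harms cannot be compared across the three arms on the same basis

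*Protocol article*

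**What the plan says.** Two sections of the protocol article deal with adverse events.

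- **Intervention.** The section states "Reasons for terminating the test: if serious adverse events occur during exercise, the test should be terminated in time". The next sentence, introduced as adverse events, gives severe hypoglycaemia with its symptoms as item 1, followed by "2) chest pain, arrhythmia, (3) breathing difficulties and asthma". The list is numbered, and nothing marks its items as examples.
- **Training intervention.** For the two treadmill arms, session data are recorded "along with any adverse events during exercise". The section then states "Exercise training will be terminated at signs of any serious adverse event (SAE), such as, severe hypoglycemia and complications", repeats the same symptoms, and ends with "breathing difficulties and asthma; pain and fatigue".

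The Guideline group section provides for one supervised session followed by weekly contact through WeChat. The data it names for weekly collection are exercise intensity and duration. Adverse events are not mentioned.

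Falls appear in several other places. The Introduction and the Discussion describe raised fall risk in this population. The Exclusion criteria remove patients with "4) a high risk of falling". The Static balance section justifies its test on the ground that "Impaired static balance is a potential risk factor for fall", and the Dynamic balance section gives the same reason. The outcome lists in the Abstract (Methods) and in Measurements contain no adverse-event, fall or injury outcome.

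**The concern.** A condensed article may leave safety definitions to the full protocol. This one does not stay silent: it sets out two lists, and they do not agree. The same symptoms are adverse events in one section and serious adverse events in the other. One list reads as complete and the other as illustrative. Staff working from this text could not tell whether a fall without any listed symptom, or a sprained ankle, has to be reported.

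The second problem is coverage. The recording rule is tied to exercise sessions in two arms. The third arm, which is the reference for the superiority comparisons, has no stated route for reporting harm.

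The Conclusion says that the results should help to identify an appropriate regimen for sedentary older patients with type 2 diabetes. That choice needs benefit and harm measured on the same footing in each arm. As written, a regimen could be favoured on HbA1c and BDNF without a comparable count of the harm that the article itself names as a risk in these patients.

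**Working it through.** No arithmetic on power or effect size applies. The check is a comparison of the texts.

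**Step 1: the two lists side by side.**

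| Feature | Intervention | Training intervention |
|---|---|---|
| Label given to the symptoms | Adverse events | Serious adverse events |
| Form of the list | Numbered, no example wording | Introduced as examples |
| Hypoglycaemia and its symptoms | Yes | Yes |
| Chest pain, arrhythmia | Yes | Yes |
| Breathing difficulties, asthma | Yes | Yes |
| Pain and fatigue | No | Yes |
| Falls, fractures, musculoskeletal injury | Not named | Not named |
| What is stopped | The test | Exercise training |

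The lists share three symptom groups. They differ in label, in form, in one item and in what is stopped. Neither names falls or injuries.

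**Step 2: where and when recording is stated.**

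| Situation | HIIT | MICT | Guideline |
|---|---|---|---|
| During exercise | Any adverse event recorded | Any adverse event recorded | Not stated |
| Between sessions | Not stated | Not stated | Not stated |

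Of the six cells, two have a stated recording rule. The guideline column stands for 330 / 3 = 110 participants.

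**Step 3: opportunity to report.** The treadmill arms have 3 supervised sessions a week for 12 weeks, which is 3 × 12 = 36 sessions per participant. After its single supervised session, the guideline arm has one remote contact a week, about 12 in all. Even under one shared definition, the treadmill arms would have about three times as many occasions to report an event. A like-for-like count therefore needs a common collection method as well as a common definition.

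**Step 4: where a fall or injury would end up.**

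- *Fall on the treadmill (HIIT or MICT).* It would probably be recorded, because the Training intervention section says any adverse event. Read strictly, the Intervention list would not count it.
- *Injury that shows as pain during a session.* It could be picked up through the pain item in Training intervention, but not through the Intervention list.
- *Fall at home, or an overuse injury between sessions, in any arm.* No stated rule covers it.
- *Fall while jogging or brisk walking in the guideline arm.* No stated rule covers it.

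**The case against.** The strongest reply is that the Training intervention section already provides for recording any adverse event during exercise. A fall from a treadmill is such an event in ordinary usage. This stands. A reader might infer from the Intervention list that falls and injuries are simply not counted in this trial, and the documents do not support that for treadmill sessions.

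A second reply is that the Intervention list directly follows a rule for ending the test, and so may be a list of stopping triggers and not a definition of what is recorded. That reading is reasonable, and the similar list beside the stopping rule in Training intervention supports it. On that reading, however, the article contains no definition of an adverse event, and its two lists of triggers still differ. Reading the list this way also does nothing for events outside sessions or in the guideline arm.

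A third reply concerns the importance of falls here. One might be tempted to call falls a leading expected harm of the training. The article does not show this. It gives no rate of falls or injuries during training, excludes patients at high risk of falling, specifies supervised walking, and cites fall prevention as a benefit of MICT. What it does establish is background fall risk in this population, and that is enough to justify naming the event.

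Finally, the absence of a harms outcome from a condensed article would be weak evidence on its own, because the full protocol or the analysis plan may supply it. This stands too. The point rests on the conflict between two sections that are printed and on the arm-specific recording rule.

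**Conclusion.** The point holds in a limited form. The Intervention and Training intervention sections are inconsistent on what an adverse event is, and neither names falls or injuries. Recording is stated only for exercise in the HIIT and MICT arms. Following the text as written gives no count of falls and injuries that is comparable across all three arms.

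The effect on the results cannot be quantified, because the documents give no event rates. In terms of coverage, one of three arms (110 participants) has no stated adverse-event recording, and time between sessions is uncovered in every arm.

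The conclusion assumes that the article's wording reflects what sites do. If the full protocol holds a single definition applied to all arms, the remaining task is to bring the article's wording into line with it. Correction is worthwhile but not critical: the primary analyses of HbA1c and BDNF are unaffected, while the comparison of harms between regimens is.

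**What to change.** 1. **One definition.** Replace the two lists, for counting purposes, with a single open definition: any untoward medical occurrence from randomisation to the week-12 visit, with falls, fractures and musculoskeletal injuries named. Define serious adverse events separately, so that the same symptoms do not carry both labels.
2. **Same collection in every arm.** Ask the same question on the same weekly schedule in all three arms: at a training session for HIIT and MICT, and through the existing WeChat contact for the guideline arm. Cover events outside sessions as well as during them. Mark events noticed only through session supervision, so that the difference in observation can be seen.
3. **List it as an outcome.** Add adverse events, including falls and injuries, as a safety outcome in the Abstract and in Measurements, tabulated by arm.
4. **Reconcile the stopping text.** The two sections also differ on the symptoms listed beside the termination rules and on what is terminated. The sponsor must reconcile these. This review takes no position on which version is right, and items 1 to 3 change what is counted, not any rule for stopping exercise.

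The cost is an amendment to one definition, a line on the session and contact forms, and an entry in the outcome lists. The downside is more events to record and report. The article says that recruitment was still under way, so the change can apply to later participants. The report should give the date of the change, because participants who finished before it may lack comparable data.

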#### Guideline group

Participants in the guideline group will perform 1-time supervised 40–50 min of dedicated training (including jogging and brisk walking) 3 times a week in addition to daily physical activity, and the rate of perceived exertion (RPE) will be set at 3–4 (Borg RPE scale: 12–16). Afterward, WeChat–a mobile-based messaging App (Tencent cop., China)- will be used to remotely monitor and supervise exercise weekly. The exercise data (intensity and duration) will be collected weekly to ensure sufficient exercise time and to encourage exercise motivation.

### Training intervention

Participants in the MICT and HIIT groups will perform exercise of different intensity on a treadmill. Exercise intensity, duration, the heart rate (HR), and blood pressure will be recorded before and after exercise, along with any adverse events during exercise. To minimize the risk of bias in the interpretation of the results, we matched the amount of exercise between the HIIT and MICT groups based on workload. Exercise training will be terminated at signs of any serious adverse event (SAE), such as, severe hypoglycemia and complications: shaking, dizziness, abnormal sweating, headache, blurred vision; chest pain, arrhythmia; breathing difficulties and asthma; pain and fatigue.

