#### HIIT group

Participants will perform training with supervision, involving walking on a flat or inclined treadmill 3 times a week. The HIIT protocol consists of a 10-min warm-up (at 50–60% of the peak HR), 10 × 1-min intervals at 85–95% of the peak HR separated by 1-min periods of active recovery (at 60–70% of the peak HR), and a final 5-min cooldown, which corresponds to the Borg RPE scale of 16–17. An HR monitor (Polar Electro, Kempele, Finland) will be used to obtain the training HR. The speed and incline of the treadmill will be continuously adjusted to ensure that each training session is performed at the prescribed HR.

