#### MICT group

Similar to the HIIT group, the participants in the MICT group will perform training with supervision, involving walking on a flat or inclined treadmill 3 times a week. Corresponding to the amount of exercise (exercise intensity × duration) of the HIIT sessions, each MICT session will consist of a 5-min warm-up period and a 5-min cooldown period at 30% of the peak HR, separated by 35 min of exercise at 65–75% of the peak HR. An HR monitor (Polar Electro, Kempele, Finland) will be used to obtain the training HR. The speed and incline of the treadmill will be continuously adjusted to ensure that each training session is performed at the prescribed HR.

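### HIIT and MICT are described as matched on intensity × duration, but in % peak HR × minutes the MICT main set is 58% larger at mid-range and the ranges do not overlap

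*Protocol article*

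**What the plan says.** The Training intervention section states that "we matched the amount of exercise between the HIIT and MICT groups based on workload", and gives protection against biased interpretation as the reason. The MICT group section says what is being equated: it introduces the MICT session with the words "Corresponding to the amount of exercise (exercise intensity × duration) of the HIIT sessions". No total, energy figure or other workload calculation is printed for either arm.

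The sessions are described as follows.

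- **HIIT group section:** a 10-minute warm-up at 50–60% of peak HR; then "10 × 1-min intervals at 85–95% of the peak HR separated by 1-min periods of active recovery", with recovery at 60–70%; then "a final 5-min cooldown", for which no intensity is given.
- **MICT group section:** 35 minutes at 65–75% of peak HR, with "a 5-min warm-up period and a 5-min cooldown period at 30% of the peak HR".

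Both arms train three times a week. Both sections say that treadmill speed and incline are adjusted throughout so that the session is done at its target heart rate.

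The Sample size calculation section makes HIIT over MICT a tested superiority hypothesis, with assumed additional effects of 0.2% for HbA1c and 1.2 ng/ml for BDNF. The Discussion explains the expected advantage of HIIT by its higher intensity.

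**The concern.** Matching is a property that the protocol claims for its design and relies on for interpretation. If the two sessions carry the same amount of exercise, a difference between the arms can be read as an effect of how intensely that amount is performed. If they do not, the arms differ in both intensity and volume, and the contrast cannot separate the two.

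The direction matters. The stated sessions put the larger amount in MICT. If extra volume helps, that would tend to work against the hypothesis that HIIT is superior. A null or small HIIT-versus-MICT difference would then have two explanations: intensity does not matter, or its benefit was offset by the smaller volume.

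A related inconsistency sits in the same section. The MICT warm-up and cooldown are set at 30% of peak HR, yet the section says that the session is held at its prescribed heart rate.

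**Working it through.** **What is being reproduced.** The claim is equality, that is, a MICT/HIIT ratio of 1.00. It is made in words, with no printed total to reproduce. The check is whether the session descriptions give that ratio.

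**Metric.** Amount = sum over segments of (% peak HR × minutes). This applies the MICT section's definition in the only intensity unit stated for both arms. The session frequency is the same, so the per-session ratio is also the weekly ratio.

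**Step 1: main sets (no assumption about the cooldown).**

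| | Low | Mid | High |
|---|---|---|---|
| HIIT, 10 recoveries | 10×85 + 10×60 = 1,450 | 10×90 + 10×65 = 1,550 | 10×95 + 10×70 = 1,650 |
| HIIT, 9 recoveries | 10×85 + 9×60 = 1,390 | 10×90 + 9×65 = 1,485 | 10×95 + 9×70 = 1,580 |
| MICT | 35×65 = 2,275 | 35×70 = 2,450 | 35×75 = 2,625 |

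Nine recoveries is the literal count if recoveries only separate ten intervals. Ten is the count more favourable to matching.

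- Mid-range ratio: 2,450/1,550 = 1.58 (10 recoveries) or 2,450/1,485 = 1.65 (9 recoveries).
- Smallest possible ratio, lowest MICT over highest HIIT: 2,275/1,650 = 1.38 (10 recoveries) or 2,275/1,580 = 1.44 (9 recoveries).

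The ranges do not overlap on either count.

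**Step 2: whole sessions at mid-range.** Let c be the HIIT cooldown intensity in % of peak HR. It is not stated; 30–70 is assumed.

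- MICT: 5×30 + 2,450 + 5×30 = 2,750.
- HIIT, 10 recoveries: 10×55 + 1,550 + 5c = 2,100 + 5c. This is 2,250 at c = 30 and 2,450 at c = 70.
- HIIT, 9 recoveries: 10×55 + 1,485 + 5c = 2,035 + 5c. This is 2,185 at c = 30 and 2,385 at c = 70.
- Ratio: from 2,750/2,450 = 1.12 to 2,750/2,185 = 1.26.

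Session length is 45 minutes for MICT and 34–35 minutes for HIIT.

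**Step 3: whole sessions at the extremes.** The lowest MICT total is 2,275 + 300 = 2,575. The highest HIIT total is 10×60 + 1,650 + 5c = 2,250 + 5c with 10 recoveries, or 10×60 + 1,580 + 5c = 2,180 + 5c with 9. They meet at c = (2,575 − 2,250)/5 = 65 or c = (2,575 − 2,180)/5 = 79. Whether whole-session ranges overlap therefore depends on an intensity that the article does not give.

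**Step 4: sensitivity to the scale.** Replace % peak HR by % heart-rate reserve, with resting HR assumed at 40–55% of peak (not in the documents). Segments below rest count as zero.

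- Main-set ratio at mid-range, rest at 40%, 9 recoveries: 35×30 / (10×50 + 9×25) = 1,050/725 = 1.45.
- Main-set ratio at mid-range, rest at 55%, 10 recoveries: 35×15 / (10×35 + 10×10) = 525/450 = 1.17.
- Whole session with a 60% cooldown: about 1.05–1.13.
- Main-set ranges are separate at rest = 40% (lowest MICT over highest HIIT 1.03–1.07) but overlap from 45% upward (0.97 and below).

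**Step 5: the 30% figure.** For an assumed peak HR of 130–160, 30% is 39–48 bpm. To reach 60 bpm, the peak would have to be 60/0.30 = 200. The inclusion criteria require age 65 or over. It is hard to see how treadmill settings could hold a participant at such a value.

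**The case against.** The strongest reply concerns the unit. The Training intervention section says only that workload was the basis, and the MICT section gives no unit for intensity in its product. Percent of peak HR is how sessions are prescribed, and multiplying it by minutes counts resting heartbeats as exercise, which favours the longer session. With resting HR at 60% of peak, the mid-range main sets become 10×30 + 10×5 = 350 for HIIT and 35×10 = 350 for MICT, a ratio of 1.00. A condensed article also need not print its workload calculation.

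Part of this stands. The 58% belongs to one metric, and a reader might infer that MICT participants truly do 58% more work; the documents do not support that. But the equality case needs a resting HR that puts the prescribed 50–60% HIIT warm-up at or below rest, so it does not rescue the matching claim. No other calculation showing equality is offered.

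Two more limits stand. A reader might infer that whole sessions cannot overlap at all. That holds only if the unstated HIIT cooldown is below 65% of peak HR (10 recoveries) or 79% (9 recoveries). A reader might also infer that the HIIT-versus-MICT comparison is confounded and therefore invalid. It is not: allocation is randomised, the programmes are the treatments, and the stated aim is to help choose a regimen. The article also presents HIIT as saving time, so a shorter session fits its rationale. An imbalance that favours MICT would not inflate a positive HIIT result, and nothing in the documents converts extra volume into HbA1c or BDNF.

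**Conclusion.** The matching statement disagrees with the session descriptions. In the only intensity unit common to both arms, the main sets differ by 58% at mid-range and by at least 38%, with no overlap; this needs no assumption about the unstated cooldown. For whole sessions at mid-range MICT is about 12–26% higher, given a HIIT cooldown of 30–70% of peak HR and 9 or 10 recoveries. On an assumed heart-rate-reserve scale MICT is still higher at mid-range for resting HR at 40–55% of peak, but by less, and the ranges mostly overlap.

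The consequence is limited to interpretation. The randomised comparison of HIIT with MICT as programmes remains valid, and the comparisons with the guideline group do not rely on the matching. What cannot be supported is attribution of a HIIT-versus-MICT difference, and especially of a null result, to intensity at equal volume.

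**What to change.** Reconcile the Training intervention, HIIT group and MICT group sections so that the matching claim and the session descriptions agree, and state the workload basis if one exists. The reconciliation should cover the 30% of peak HR warm-up and cooldown against the statement that sessions are held at their prescribed heart rate. This review takes no position on which prescription is right.

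If the sessions stand and no workload basis shows equality:

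- delete the matching claim;
- describe HIIT versus MICT as a comparison of programmes that differ in intensity and volume;
- report delivered intensity × time by arm, from the exercise intensity and duration already to be recorded and, where traces are saved, from the heart-rate monitors.

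The cost is mainly wording and one descriptive table, with a weaker mechanistic claim for HIIT over MICT. There may be some extra data handling: the Training intervention section places its recording before and after exercise, and the arm sections use the monitors to obtain training heart rate without saying that traces are kept. Stored heart-rate × time data cannot be assumed to exist, so the traces may have to be saved.
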